#### Quality control and data monitoring

2.9.1

This study will be monitored by Korean Medicine Clinical Trial Center, a CRO company that consults with institutions conducting clinical trials to ensure compliance with protocol and K-GCP. During monitoring, crosschecks will be conducted with the evidence to ensure that the documents (trial master files, CRF, informed consent forms, and adverse events reports) are complete and clear.

#### Research ethics approval

2.9.2

This trial has received complete ethical approval from the Ethics Committee of Catholic Kwandong University International St. Mary's Hospital (IS20OISE0085).

#### Protocol amendments

2.9.3

The investigators who want to perform protocol amendments should first discuss it with the principal investigator, and they can change the protocol after obtaining approval from the IRB. However, when a dangerous situation occurs and immediate care is needed, the protocol change will be reported to the IRB at a later time.

#### Post-trial care

2.9.4

If the patients experience unexpected accidents or injuries, the patients will receive appropriate medical care at the Catholic Kwandong University, International, St. Mary's Hospital. Additionally, appropriate compensation will be made by the insurance company, according to the patient compensation rules of the trial.

## Discussion

3

Acupotomy is a treatment method of inserting a needle with a scalpel-shaped tip into a blood vessel, light muscle, or a tender point of the body. The needle then helps to detach the adhesion sites of muscles and ligaments with low energy and blood to treat relevant diseases. This treatment method is widely used in China and Korea. In particular, acupotomy is conducted to treat lumbosacral radiculopathy such as lumbar disk herniation and lumbospinal canal.^[4–13]^ In Korea, NBT is generally performed 3 times at two-week intervals for patients with lumbosacral radiculopathy. Patients who continuously experience pain while waiting for the next NBT treatment voluntarily undergo Korean medicine treatment such as acupotomy and acupuncture.

Although many patients with lumbosacral radiculopathy undergo Korean medicine treatment with NBT, there are no studies on combination treatment of acupotomy and NBT. Thus, there is a need for studies on the objective efficacy, safety, and economic feasibility of acupotomy and NBT combination treatment.

In this clinical study, patients whose pain will be improved by less than 50% and will have a NRS score greater than five after the first NBT will be included in order to select patients with weak response to NBT. This was to test the hypothesis that acupotomy, which has greater stimulation effects compared with acupuncture, will cause biomechanical effects, thereby leading to synergistic effects with the biochemical effects of NBT in patients with a weak response to NBT.

Objective evidence for the synergistic effects, safety, and economic feasibility of the combination treatment of NBT and acupotomy will suggest a new alternative treatment that can be used together with NBT, a standard treatment method. This would bring several direct benefits, such as reduced rate of surgeries to the patients.

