**Methods/design::**

This is an open-label, parallel, assessor-blinded, randomized controlled trial, which will include 50 patients with lumbosacral radiculopathy. After patients voluntarily agree to participate in the study, they will be screened, and will undergo necessary examinations and tests according to the protocol. Those who satisfy the selection criteria will be randomly assigned to either the NBT + acupotomy or NBT groups in a 1:1 ratio. Both groups will undergo 2 NBTs once every 2 weeks from 1 week after the screening test. The treatment group will receive additional acupotomy twice a week for 4 weeks. The primary endpoint is the Oswestry Disability Index, whereas the secondary endpoints are the Numeral Rating Scale, European Quality of Life 5-dimension, McGill pain Questionnaire, Roland-Morris Disability Questionnaire, safety assessment, and economic feasibility evaluation. The measurements will be made at 0, 2, 4, and 8 weeks.

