Therefore, herein, we expect that the biochemical effects of NBT and the biomechanical effects of acupotomy will lead to a synergistic effect, and thereby propose to conduct a preliminary clinical study using the following protocol. The proposed study is expected to greatly contribute to the Korean and modern medicine combination treatment for lumbosacral radiculopathy and have important clinical implications.

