### Objective

1.1

The study aims to verify the hypothesis that the concurrent use of a deeply inserted acupotomy needle and NBT is more effective, safe, and cost-effective for lumbosacral radiculopathy than NBT alone.

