### Sample size calculation

2.3

This is a practical clinical study to assess the effects NBT and deeply inserted acupotomy combination treatment on lumbosacral radiculopathy.

In a previous pilot RCT that compared the therapeutic effects of deeply inserted acupotomy and general acupuncture in lumbar disc herniation patients,^[14]^ considering a 20% drop-out rate, a total of 50 patients (25 each in the acupuncture and deeply inserted acupotomy groups) were included.

In another RCT that compared the effects of deeply inserted acupotomy and general acupuncture in lumbar disc herniation patients,^[15]^ a total of 40 patients (20 each in the acupuncture and deeply inserted acupotomy groups) were included.

The phase 1 preliminary clinical study that will be conducted aims to estimate the mutual effects of NBT and deeply inserted acupotomy combination treatment and assess whether the combination treatment is effective and safe compared with conventional treatment. Thus, the study must be conducted with a minimum number of patients within the limit that satisfies the study purpose. Currently, there is no previous study that has provided the same intervention. Therefore, based on previous studies that provided similar treatment interventions and involved disease groups as in our study, 20 patients were included in each group. Considering a dropout rate of 20%, a total of 50 patients (25 patients in each group) was set as the target sample size.

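### The Discussion and the sample-size section announce a test of synergy between acupotomy and NBT, but the two-arm design estimates only the effect of acupotomy added to NBT

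*Protocol article*

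**What the plan says.** The protocol article states its purpose in two ways.

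- **As an add-on comparison.** Section 1.1 (Objective) gives the hypothesis that concurrent acupotomy and NBT "is more effective, safe, and cost-effective for lumbosacral radiculopathy than NBT alone". The second half of the aim sentence in section 2.3 also asks how the combination compares with conventional treatment.
- **As a test of synergy.** Section 3 (Discussion) explains that weak responders are selected in order to test whether acupotomy "will cause biomechanical effects, thereby leading to synergistic effects with the biochemical effects of NBT in patients with a weak response to NBT". It then names as the expected product "Objective evidence for the synergistic effects, safety, and economic feasibility of the combination treatment of NBT and acupotomy". The first half of the aim sentence in section 2.3 says the study "aims to estimate the mutual effects of NBT and deeply inserted acupotomy combination treatment".

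The Introduction also mentions synergy, but only as an expectation: "we expect that the biochemical effects of NBT and the biomechanical effects of acupotomy will lead to a synergistic effect".

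On design, the Abstract says patients are "randomly assigned to either the NBT + acupotomy or NBT groups in a 1:1 ratio". Section 2.6 confirms that every group receives NBT. Section 2.9 defines the primary efficacy contrast as the between-group difference in least-squares mean ODI change from baseline to week 4, with baseline ODI as covariate.

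**The concern.** In its usual statistical sense, synergy means that two treatments together do more than the sum of what each does separately. Judging it requires knowing what acupotomy does without NBT, and no randomised patient is in that position. The Discussion nevertheless presents synergy as the hypothesis under test and as something the results will evidence.

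What is at stake is the conclusion. If the text stands, a positive ODI difference could be reported as evidence of synergy when it fits simple addition, or even a partial overlap of the two treatments, just as well. A statistical analysis plan cannot repair this, because no analysis recovers groups that were never randomised.

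**Working it through.** **The plan's own figure.** Section 2.3 takes 20 patients per group from earlier similar trials and allows for 20% dropout: 20 / (1 - 0.20) = 25 per group, 50 in total. This reproduces. The section states no effect size, SD or power, and the point below does not depend on the sample size.

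**Inputs from the documents.** Two arms, NBT and NBT + acupotomy (Abstract; section 2.2); NBT in both (section 2.6); one between-group contrast on ODI change (section 2.9).

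**Model.** Express benefit as points of ODI reduction and write the mean benefit in a group as

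μ + N·(NBT given) + A·(acupotomy given) + I·(both given),

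where N and A are the separate effects and I is the interaction. I > 0 is synergy, I = 0 is plain addition, and I < 0 is less than additive.

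- NBT arm: μ + N
- NBT + acupotomy arm: μ + N + A + I
- Difference: (μ + N + A + I) - (μ + N) = **A + I**

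The trial estimates the sum A + I and nothing that splits it.

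**Formal check.** The design matrix for the two arms, with rows (1,1,0,0) and (1,1,1,1), has rank 2. Adding the row for I, (0,0,0,1), raises the rank to 3, so I is not estimable however many patients are enrolled. With all four groups (neither, NBT only, acupotomy only, both) the rank is 4 with and without that row, so I would be estimable.

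**Illustration.** All values are assumed, since the documents give none: μ = 0, N = 5.

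| Scenario | A | I | NBT arm | Combination arm | Difference |
|---|---|---|---|---|---|
| Pure synergy | 0 | +8 | 5 | 5 + 0 + 8 = 13 | 8 |
| Part synergy | 3 | +5 | 5 | 5 + 3 + 5 = 13 | 8 |
| Plain addition | 8 | 0 | 5 | 5 + 8 + 0 = 13 | 8 |
| Less than additive | 12 | -4 | 5 | 5 + 12 - 4 = 13 | 8 |

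The expected means are identical in every row, so the trial cannot tell these cases apart.

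**Why adding arms is not the answer here.** For 80% power at a two-sided 5% level, in SD units and by normal approximation, take the 40 evaluable patients that section 2.3 implies:

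- Two arms of 20: (1.960 + 0.842) × √(2/20) ≈ 0.89 SD is detectable.
- Four groups of 10, interaction contrast: (1.960 + 0.842) × √(4/10) ≈ 1.77 SD.

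A factorial trial of this size could detect only an interaction twice as large as the main comparison can. To detect an interaction of the same size as a given two-arm effect takes about four times as many patients.

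**The case against.** The strongest reply is that the operative trial is already the right one. The only section headed Objective states the add-on comparison, the analysis section tests exactly that, and no endpoint, test or decision rule uses synergy. This stands: neither the objective nor the primary contrast needs changing. A reader might infer from the synergy language that the primary comparison is invalid; the documents do not support that.

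A second reply is that synergy and mutual effects are loose words for two treatments with complementary targets, since the article never defines either term. That is possible, most plausibly for the phrase in section 2.3. But the Discussion makes synergy the hypothesis being tested and promises objective evidence of it. If only added benefit is meant, the text should say so, and the correction is easier still.

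Other stronger readings are tempting and should be left aside:

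- *That the trial claims an effect particular to weak responders, and so needs good responders for comparison.* The Discussion names weak responders as the population studied. It does not say the effect is absent or smaller in others.
- *That the trial sets out to demonstrate a biomechanical mechanism.* The mechanism is part of the reasoning behind the hypothesis, but no mechanistic endpoint is planned and none is among the evidence the Discussion expects. Non-specific effects in an open-label trial with a patient-reported outcome are a separate question.
- *That the Introduction and Abstract must also change.* There synergy is an expectation and a reason for doing the study, which is legitimate.
- *That a false claim of synergy will be published.* That is a forecast; the text permits such a claim but does not make it inevitable.

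**Conclusion.** The point holds for two places: the hypothesis and expected evidence in the Discussion, and the mutual-effects phrase in section 2.3. Both attribute to the trial a property its design does not have. The trial identifies A + I, the effect of acupotomy added to NBT; the interaction I is not identified at any sample size.

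The algebra rests only on NBT being given in both arms and on synergy meaning more than the sum of the separate effects. The ODI values in the table are assumptions that show the range of interactions compatible with one result; they are not estimates for this trial.

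The defect limits what may be concluded. It does not affect the validity of the comparison with NBT alone, so it is a correction of the stated aim and conclusion rather than of design or analysis.

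**What to change.** 1. **Section 2.3:** replace the mutual-effects wording with *estimate the additional effect of acupotomy given with NBT*. Leave the rest of the sentence as it is.
2. **Section 3, Discussion:** restate the tested hypothesis and the expected evidence as the added effect of acupotomy on top of NBT in patients with a weak response to a first NBT. Keep synergy as the rationale, and add one sentence saying that, because both arms receive NBT, the trial cannot establish it.

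Sections 1 and 1.1 and the primary analysis in section 2.9 stay as they are. No arm, patient, endpoint or analysis is added. The cost is a less ambitious claim.
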